## Analytic plan

### HIV, HCV, and OUD cascades of care

The primary outcome of this project is to assess the difference in time to initiation of PrEP or ART between PN and MHU groups

PrEP initiation will be measured as the date of self-reported initiation within the 6-month intervention period as has been used in other studies of PrEP uptake [65]. Self-reported initiation will be triangulated with prescribing data from the medical record and pharmacy fill date; the same approach will be used to assess post-release ART re-initiation/continuation. If participants are unable to be contacted, when appropriate, medical visit appointment attendance with community providers will be assessed. We will continue to follow individuals if they are returned to custody (with statistical models adjusting for incarceration time, as appropriate).

Time to post-randomization initiation of PrEP/ART will be analyzed as intention-to-treat analyses including all persons fully enrolled in the project using Kaplan–Meier estimates and adjusted Cox proportional hazards models, adjusted for relevant covariates. The effect of treatment on the outcome will be described using the estimated coefficients of the treatment term in the model, the corresponding hazards ratio, and 95% confidence interval. Kaplan–Meier estimates will be used to generate and plot survival curves over time in the PN and MHU groups. The inferences from analyses with missing data are valid provided that they are “missing at random” [66]. ‘Missing at random’ (i.e., does not depend on the value of the unobserved outcome) is un-testable in most medical research and in our study as well. Sensitivity analysis will assess the effect of the assumption of missing ‘at random’ on the inference.

PrEP Cascade-based outcomes will be evaluated as the proportion of participants who initiate PrEP and are on PrEP at end of intervention [67]. These will be calculated as overall percentages and stratified by study arm. Evidence of PrEP adherence will be assessed by DBS testing and defined as a tenofovir-disoproxil diphosphate (TFV-DP) level > 700 fmol/punch [61] at 6 months, reflecting cumulative dosing over 6–8 weeks and consistent with 4 or more doses of PrEP per week [62]. This threshold has been commonly used as the level required to achieve adequate HIV protection, however, as the level of adherence that is required for HIV protection among people who inject drugs is less clear, and there are limited data on measures of PrEP adherence among people who inject drugs [62, 68]. We will triangulate multiple adherence measures: TFV-DP DBS levels as a continuous outcome; point of care TFV-DP urine testing, which measures recent (past 48 h) dosing [69], self-reported PrEP adherence via VAS [50], and pharmacy refill data. The proportion of those tested for HIV with negative results using rapid point of care testing over time will be calculated.

The HIV care cascade will include: HIV incidence for those who seroconvert during the course of the study; post-incarceration ART initiation and adherence: ART initiation (or continuation) post-release defined as time to self-reported initiation of ART after release from the justice system. ART initiation will be triangulated using prescription date data from the community-based medical record (either via PN referral or via MHU visit) and prescription fill date for ARTs; ART adherence is defined as the proportion who have an ART prescription and who are retained on ART, which will be assessed via self-report as well as DBS testing for TDF- and TAF-based regimens; Retention in HIV ART care is defined as attending 2 or more visits in 6-months post-enrollment and will be assessed via self-report; HIV viral suppression will be assessed as the proportion who maintain or achieve viral suppression defined as HIV viral load (VL) < 200 copies/mL at 6 months [8, 10]; HIV Risk Behaviors will be assessed for shared of injection equipment, as well as other substance use, and sexual risk behaviors over time. The HIV care cascade will be calculated overall and stratified by arm.

HCV cascade of care cascade will be assessed as the proportion who have a reactive rapid point of care HCV test with confirmatory reflex HCV VL; the time to linkage for and HCV treatment appointment, and time to receiving HCV direct acting antiviral treatment during the 6 month intervention; the proportion eligible who complete treatment; of those, the proportion who achieve sustained virologic suppression at week 12 (undetectable HCV VL); and of those who achieve sustained virologic suppression [70, 71], the proportion who have HCV re-infection at 12 months. The HCV care cascade will be calculated overall and stratified by arm.

OUD/SUD outcomes and cascades of care will include the proportion who have a current or past diagnosis of SUD (including stimulant and opioid use) by (a) proportion of monthly negative versus positive/missing urine samples, (b) self-reported days of opioid and injection drug use using the timeline followback and other drugs and alcohol using the TCU Drug Screen 5 and Opioid Supplement [53], and c) and percent of opioid and/or stimulant-free months (0–6). In addition, we will track non-fatal and fatal overdose events, addiction treatment participation, and linkage to and retention on MOUD using a brief version of the Treatment Services Review [72] that records type and dose of MOUD and behavioral health. These cascades will be calculated overall and stratified by arm.

For repeated (longitudinal) continuous or categorical outcomes such as adherence and retention in care, longitudinal generalized mixed effect models (MEM) will be fit. The MEMs allow adjustment for potential unequal or time-varying variances. Different link functions will be used depending on each outcome variable: logit-link for binary and categorical outcomes, log-link function for right-skewed distributions, and identity-link function for normally distributed outcomes. The generalized estimation equation structure will be added to model within-subject correlations over time as an autoregressive AR [1] process. Each model will include the main effect of the predictor of interest, main effect of time (baseline, months 1, 3, 6, and 12), their interaction (if the predictor is observed and desired to analyze over time), and relevant covariates (if appropriate). Time to PrEP/ART uptake will be analyzed either as a continuous or categorical predictor if changes over time are not assumed to be linear. Associations of predictors with secondary continuous or categorical outcomes that are not longitudinal will be analyzed using generalized linear models fit similarly as above. However, each model will include the main effect of the predictor of interest and relevant covariates only.

Moderation statistical models will be used to determine the effect of randomization to PN versus MHU arms among subpopulations of the sample based on the demographic and baseline characteristics selected as moderators. These characteristics include age, gender, primary substance used, race, ethnicity, and living in an urban or rural setting. We will estimate the moderation effect on primary outcome using similar models noted above with the inclusion of moderator by treatment interactions in the Cox proportional hazards model. Regardless of the significance of the interaction term, we will use the model to estimate the 95% confidence interval of the treatment effect for each level or category of the moderator variable, or the treatment effect at selected values of the moderator variable, if continuous. The moderator analyses are exploratory and hypothesis generating, but significant moderator effects can be useful in planning future efforts at implementation linkage to and receipt of HIV prevention and treatment services for persons who use substances and are at risk of acquiring or are living with HIV released to the community from the justice system. By identifying subgroups who receive less benefit, modifications to the implementation strategy can be performed to achieve better effects in those subgroups, therefore improving patient care.

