### Sample size and power calculations

The primary outcome analysis will compare the effectiveness of using either PN or MHU, with the outcome being the length of time it takes for study participants to take their first dose of recommended medications (ART for PLH or PrEP for those at risk for HIV) post randomization. We hypothesize that the MHU arm will be superior to the PN arm, given the convenience and flexibility of the delivery of services. We expect that around 5% of our sample will be PLH and 95% will be at risk for HIV. We also expect 80% retention at the 6-month follow-up assessment. Using SAS PROC Power [26] for comparing two survival curves with log-rank test, we found that 864 recruited participants are needed (evenly distributed across study sites, n = 216 per project site; to achieve a sample size of 689 at 6-month follow-up) under the assumptions of alpha = 0.05 and 80% power to detect a hazard ratio (HR) between 1.25 and 1.30 for main effects of treatment arms. The effect size is based on the literature on PLH referred to ART and people at risk for HIV referred to PrEP. For PLH, 64% of the patients in the treatment condition (designed to facilitate initiation of ART) compared to around 51% of patients in standard care within 10 months [27], yielding hazard ratio of 1.25 comparing the MHU group to the PN group.

For the those at risk for HIV and at high risk of contracting sexually transmitted infections (STIs), the drop-off between PrEP referral to PrEP initiation may be as high as 90% [27–29]. To our knowledge, there are no published studies of PrEP uptake among justice-involved populations, although several papers describe low knowledge of PrEP and moderate levels of interest in taking PrEP among people who inject drugs and justice-involved persons [30–33]. A recent paper indicated that 25% of incarcerated persons reported being interested in taking PrEP after release [30]; given actual uptake generally is lower than reported intention, we assumed that the uptake would be between 10% in the PN group and 20% at best in the MHU group given easier access.

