### Healthcare initiation, adherence, and retention of care

Data will be collected to create treatment cascades associated with HIV, PrEP, HCV, MOUD, and STI testing, diagnoses, treatment, and care. Diagnoses and sero-conversion of HIV, HCV, and STIs will be assessed through medical history at every visit and via biological tests noted below. Based on diagnoses and current medications, time to linkage, initiation, or continuation of ART, PrEP, HCV, MOUD, or STI care and medications will be assessed from time of release from justice-based facilities, after randomization for those in the community, or upon diagnosis throughout the 12-month study participation period. Adherence to ART, PrEP, HCV, and STI treatments will be assessed using a visual analog scale (VAS [50]) for daily medications. Biological measures described below will assist with the evaluation of ART and PrEP adherence. For PLH at time of randomization the percent who maintain or achieve HIV viral load < 200 copies/mL at 6 months [51, 52] will be collected. Persistence on medication will be determined by assessing if medication was discontinued and reason for discontinuation, including successful cure of the infection if applicable. Attendance to medical visits will be confirmed with community providers and the MHU.

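### Current users stay in the primary risk set and ART continuation counts as initiation, so people already on treatment in the community modestly dilute the hazard ratio

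*Protocol article*

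**What the plan says.** All references are to the protocol article.

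- **Event.** *Sample size and power calculations* defines the outcome as "the length of time it takes for study participants to take their first dose of recommended medications", counted from randomization. *Project aims* starts the clock at release for people in custody and at randomization for people enrolled in the community.
- **ART continuation.** *HIV, HCV, and OUD cascades of care* sets out self-report, prescribing and pharmacy-fill data for PrEP initiation, then says "the same approach will be used to assess post-release ART re-initiation/continuation". The care-cascade text in that section makes it a single measure: "ART initiation (or continuation) post-release defined as time to self-reported initiation of ART after release from the justice system".
- **PrEP.** The primary-analysis text speaks only of initiation. Continuation of PrEP appears only in the general list of measures: "Based on diagnoses and current medications, time to linkage, initiation, or continuation of ART, PrEP, HCV, MOUD, or STI care".
- **Who is analysed.** The primary analysis is intention-to-treat on everyone who completed enrolment. None of the four exclusions under *Eligibility criteria* concerns current ART or PrEP, and people with HIV may qualify by chart review. *Study design and settings* expects some participants to need continued rather than first access to ART.
- **Numbers of users.** None is given. *Background* describes PrEP use among HIV-negative people in this population as unusual.

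**The concern.** The stated rules combine into a definition that some participants meet as soon as follow-up starts. For someone living in the community and already taking ART, the next daily dose is a first dose after randomization, whichever arm they are in. Such an event says nothing about how quickly navigation or the mobile unit gets a person started.

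The design assumptions describe new starts: PrEP uptake of 10% v 20%, and an ART figure of 51% v 64% from an intervention aimed at initiation. The event analysed is therefore broader than the event that was powered. Null events at the start of follow-up move the hazard ratio toward 1 and cost power. *Study design and settings* also describes the comparison as one of noninferiority, and on that reading a pull toward 1 would not be conservative.

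People with HIV are expected to be only about 5% of the sample. What counts, though, is their share of events, and that share is larger because PrEP uptake is expected to be low.

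**Working it through.** **Inputs from the protocol article.** N = 864; 5% with HIV (43.2 people) and 95% at risk (820.8); PrEP uptake 10% v 20%; ART 51% v 64% (quoted for 10 months, used here as six-month rates, which is an assumption); 1:1 allocation; 80% retention; six-month event window. The share already on treatment is assumed.

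**The plan's own figure.** The plan wants "to achieve a sample size of 689 at 6-month follow-up". 689/0.80 = 861.25, close to the 864 recruited, so the attrition step reproduces. The stated basis is "alpha = 0.05 and 80% power to detect a hazard ratio (HR) between 1.25 and 1.30". Schoenfeld's formula, 4(1.96 + 0.8416)²/(ln HR)², requires 631 events at HR 1.25 and 457 at HR 1.30. The 5%/95% mix gives 689 × (0.95 × 0.15 + 0.05 × 0.575) ≈ 118 events, or about 30% power at HR 1.30. That the hazard-ratio step does not reproduce is a separate and larger problem. It is why dilution is shown below under two sets of assumptions.

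**Share of events, before dropout.**
- PrEP: 820.8 × 0.15 = 123.1 events.
- ART, no current users: 43.2 × 0.575 = 24.8 events.
- Half of people with HIV already on ART: 21.6 null events and 12.4 new starts; null share 21.6/157.1 = 14%.
- All already on ART: 43.2 null events; null share 43.2/166.3 = 26%.

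**Hand check of the dilution.** Under exponential times the PrEP hazard ratio is ln 0.80/ln 0.90 = 2.12 (log 0.7505) and the ART hazard ratio is ln 0.36/ln 0.49 = 1.43 (log 0.359). Weighting log hazard ratios by events, with null events contributing 0:
- No users: (92.4 + 8.9)/148.0 = 0.685, HR 1.98.
- Half: (92.4 + 4.5)/157.1 = 0.616, HR 1.85.
- All: 92.4/166.3 = 0.556, HR 1.74.

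**Simulation.** Unadjusted Cox and log-rank, 3,000 runs per scenario, 20% uniform loss over six months. Current users have an event in the first day regardless of arm. Monte Carlo error on power near 94% is √(0.94 × 0.06/3000) ≈ 0.4 points.

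| Already on treatment | HR, plan's uptake rates | Power | HR, design HR 1.30 with 51% control rate for all | Power |
|---|---|---|---|---|
| None | 1.96 | 97% | 1.30 | 78% |
| Half of people with HIV | 1.82 | 94% | 1.28 | 75% |
| All people with HIV | 1.70 | 91% | 1.27 | 72% |
| Half of people with HIV, plus 5% of HIV-negative on PrEP | 1.57 | 85% | 1.25 | 68% |

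A separate simulation under the plan's uptake rates gave HR about 1.95, 1.82 and 1.70 with power about 97%, 94% and 90% for the first three rows. Restricting to non-users brought power back to about 96–98%.

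**Reading the restored hazard ratio.** After removing users, the event-weighted figure is 96.9/135.5 = 0.715 (HR 2.04) when half of people with HIV are removed, and 2.12 when all are. Both exceed 1.95 because the remaining group has fewer people with HIV, for whom the assumed effect is smaller. That part of the rise is case mix, not recovered dilution.

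**The case against.** The strongest reply is that continuation is a legitimate target. *Background* says engagement in HIV care and viral suppression fall sharply after release, and that people prescribed PrEP often lose it on incarceration. The cascade text counts ART continuation from release and checks it against the community record and fill date. For someone treated in custody, that record marks the linkage step that the two arms are meant to influence. This stands. A reader might infer that every current user contributes an immediate event unrelated to arm; the documents do not support that for people leaving custody.

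A second reply also stands in large part. PrEP continuation is not in the primary event definition, and the general measures text says that current medications inform what is assessed. The 5% baseline PrEP use in the last table row is half the uptake expected in the navigation arm, and nothing in the documents supports it. A reader might infer from that row that power is seriously threatened; the ART route alone does not show this.

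A reader might also infer bias because randomization is stratified by site and not by HIV status. Chance imbalance in about 43 people is ordinary sampling error, already allowed for in the type I error rate, and the Cox model is to be covariate-adjusted.

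What these replies do not answer is the participant enrolled in the community and already taking ART. No release interrupts that person's treatment, and the stated definition is met at once. The Texas sites (2 × 216 = 432 participants) recruit mainly through health care and substance use treatment facilities, so community enrolment is not marginal, although the number on ART there is unknown. Nor is this a detail simply left to an analysis plan: the article itself states the event, the merger with continuation and the analysis set.

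**Conclusion.** The point holds for participants already taking the indicated medication in the community at time zero. Their events fall almost immediately in both arms and pull the primary hazard ratio toward 1. It does not hold for all people on ART in custody.

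The size is modest. Under the plan's uptake rates the ART route costs about 3 points of power if half of people with HIV are current users and about 6–7 if all are, leaving power at 90% or above. With the design hazard ratio of 1.30 and a 51% control rate, the cost is again about 3 to 6 points, but from a start of 78%. The all-users row is an upper limit for the ART route at 5% prevalence, because it treats custody participants as if they too had immediate events. Larger losses need baseline PrEP use that the protocol calls atypical.

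These figures rest on assumed shares of current users, on exponential event times, and on reading the 10-month ART rates as six-month rates. The direction does not depend on the exact shares, provided that some participants are current users in the community and the intervention affects new starts.

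**What to change.** 1. Classify current use of the indicated medication (ART or PrEP) at or before randomization. Treatment history is already collected at baseline.
2. Restrict the primary Cox and log-rank analysis of initiation to participants not already taking that medication in the community at time zero, and stratify or adjust by HIV status.
3. For people on ART in custody, date the event by the first community prescription or fill after release.
4. Report continuation as a separate outcome.
5. Keep the analysis of everyone enrolled as a sensitivity analysis.

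The cost is wording and one baseline flag. At most some tens of participants leave the primary risk set. Because the restriction uses information fixed at or before randomization, the randomized comparison remains valid. The estimand does change: it narrows to initiation, and the protocol should say so. A hazard ratio from the restricted set should not be read against the all-enrolled one as a pure measure of dilution, because the case mix differs.

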### Mental health, stigma, social functioning, pain, and quality of life

Pre-justice involvement mental health diagnoses will be collected. Current depressive symptoms will be assessed using the PHQ9 [57, 58] at baseline and months 3, 6, and 12. Social functioning, quality of life, and pain will be assessed using the PROMIS [59] at baseline and month 3, 6, and 12 visits. Stigma associated with being a person who uses or used substances will be assessed using a harmonized scale from the HIV Prevention Trials Network INTEGRA initiative (HPTN 094) at the same time points.

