### Implementation, feasibility, and adaptation

We will examine changes across time of feasibility, acceptability, adoption, and sustainment for both interventions. The Proc Mixed random intercepts multi-level repeated measures model will be used where variations in changes are estimated and the effects of time, study arm (PN vs. MHU), and their interaction will be tested as fixed effects. Baseline measures of each dependent measure will be used in the analyses as covariates.

Convergence of the data will bolster validity in the findings by merging qualitative and quantitative data to provide insight into the effectiveness of the interventions. This is especially important to promote validity for implementation science studies that typically use nested designs with a small sample of communities [73]. We will (1) assess intra-cluster (community) correlations (all conditions); (2) summarize (descriptive stats) individual and community characteristics for each intervention arm (numbers analyzed, the average cluster size, cluster characteristics, and important staff/client characteristics). If differences exist between conditions, the variables will be included as selected covariates in analytic models. An intention-to-treat approach will be used whereby observations are analyzed in their intended condition. Also, protocol implementation measures will be recorded, summarized, and reviewed monthly in order to inform real-time adjustments (e.g., changes in protocols if adherence to the protocol is not met). At project end, difference in proportions will be calculated as a measure of effect, and large-sample 95% confidence limits calculated as a measure of precision.

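### For arm comparisons on outcomes with a pre-randomisation baseline, the longitudinal secondary models should adjust for that baseline, not count it as an outcome visit with a free arm effect

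*Protocol article*

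**What the plan says.** In the protocol article, Analytic plan, under HIV, HCV, and OUD cascades of care, repeated outcomes are to be fitted with generalized mixed effect models. The terms are set out as follows.

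- "Each model will include the main effect of the predictor of interest", together with "main effect of time (baseline, months 1, 3, 6, and 12), their interaction". Baseline is therefore one of the levels of time.
- The interaction is conditional: "if the predictor is observed and desired to analyze over time".
- Other covariates are left open as "relevant covariates (if appropriate"). The baseline value of the outcome is not named.
- The correlation structure is meant to "model within-subject correlations over time as an autoregressive AR [1] process". No value is given.
- The models are introduced for "continuous or categorical outcomes such as adherence and retention in care".

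Under Implementation, feasibility, and adaptation, the repeated-measures model for the implementation outcomes also has time, arm and their interaction, but there "Baseline measures of each dependent measure will be used in the analyses as covariates".

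Several participant outcomes do have an interview baseline. One example is in the section on mental health, stigma, social functioning, pain and quality of life: "Current depressive symptoms will be assessed using the PHQ9 [57, 58] at baseline and months 3, 6, and 12". That section gives the same time points for PROMIS and the stigma scale. Table 1 also marks a baseline for HIV risk behaviors, the timeline followback, the TCU Drug Screen and craving.

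**The concern.** If baseline is a level of time, it is a response occasion. With arm as the predictor, the arm main effect then leaves the arm difference at baseline free to be estimated. These baselines come from interviews completed before randomisation, so that difference is zero in expectation, and estimating it spends information.

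What follows depends on which contrast is reported:

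- With the interaction, the arm-by-time terms are change-from-baseline contrasts and carry the noise of the baseline measurement. An arm difference read off at one visit makes no use of the baseline at all.
- Without the interaction, one arm effect is spread over all visits, including one at which no effect is possible. This pulls the estimate toward no difference between PN and MHU.

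The baselines are collected in any case, so the information is already paid for.

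**Working it through.** **Inputs.** The article gives no variance, correlation or power for these models, so there is no figure of its own to reproduce. Its 80% power and 689 participants at month 6 belong to the primary log-rank calculation. The correlation ρ between baseline and follow-up is an assumption, taken here as 0.3 to 0.7. The formulas are for a continuous outcome with an identity link, equal variances over time, 1:1 allocation and complete data.

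**Step 1: variance of each arm contrast**, in units of 2σ²/n with n per arm.

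- Arm difference at a visit, baseline arm difference free: 1
- Change-from-baseline contrast: 1 + 1 − 2ρ = 2(1 − ρ)
- Baseline as covariate, or arms constrained equal at baseline: 1 − ρ²

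**Step 2: precision lost**, meaning the share of the written contrast's variance that adjustment would remove.

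- Change contrast: 1 − (1 − ρ²)/[2(1 − ρ)] = 1 − (1 + ρ)/2 = (1 − ρ)/2
- Visit contrast: 1 − (1 − ρ²) = ρ²

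| ρ (assumed) | Change variance | Visit variance | Adjusted variance | Loss, change | Loss, visit |
|---|---|---|---|---|---|
| 0.3 | 1.40 | 1.00 | 0.91 | 35% | 9% |
| 0.5 | 1.00 | 1.00 | 0.75 | 25% | 25% |
| 0.7 | 0.60 | 1.00 | 0.51 | 15% | 49% |

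The two losses run in opposite directions as ρ rises and meet only at ρ = 0.5, where the standard error is inflated by √(1/0.75) = 1.155. Both are above zero for any ρ between 0 and 1.

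**Step 3: under the planned AR(1).** With visits at 0, 3, 6 and 12 months and correlation decaying by visit order, month 6 is two steps from baseline.

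- Adjacent-visit correlation 0.5: baseline-to-month-6 correlation 0.5² = 0.25; losses 0.25² = 6% (visit) and (1 − 0.25)/2 = 38% (change).
- Adjacent-visit correlation 0.7: 0.7² = 0.49; losses 24% (visit) and 26% (change).

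Generalised least squares for the full four-visit model gave the same values.

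**Step 4: interaction omitted.** Under AR(1), the generalised least squares estimate of a constant arm effect weights the two end visits by 1 and the two middle visits by 1 − ρ (here ρ is the adjacent-visit correlation). Baseline is an end visit, so its share is 1/[2 + 2(1 − ρ)] = 1/(4 − 2ρ). If the true effect is 0 at baseline and 1 at months 3, 6 and 12, the estimate is 1 − 1/(4 − 2ρ):

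- ρ = 0.3: 1 − 1/3.4 = 0.71
- ρ = 0.5: 1 − 1/3.0 = 0.67
- ρ = 0.7: 1 − 1/2.6 = 0.62

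**Step 5: which outcomes are touched.** Table 1 marks visual analog adherence and engagement in care only from month 1, and tenofovir measures only from month 3 or later. They have no baseline, so nothing is lost there. The enrollment section lets biological baselines follow randomisation for some participants in custody, so the point is limited to interview baselines.

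**The case against.** The strongest reply is that the section is a generic template. It speaks of a predictor of interest, never names arm, and goes on to treat time to PrEP/ART uptake as a predictor. The bracketed visits repeat the trial's five research visits, and no measure in Table 1 is collected at both baseline and month 1, so the list cannot be the literal time factor of any one of those outcomes. The open covariate clause does not exclude a baseline value. Baseline as a response is a standard, valid model, and a condensed article may leave such detail to the analysis plan.

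Much of this stands. The point has to be conditional on arm being the predictor, and with the interaction included there is no bias. What does not fall away is that the article lists baseline as a time level in each such model. A value that is already in the response cannot sensibly serve as a covariate as well, so the covariate clause is no remedy unless the time list changes.

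Four stronger readings are tempting, and the document does not support them.

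- A reader might infer that about a quarter of the precision is lost. That is the result at an assumed correlation of 0.5, and the article gives none.
- A reader might infer that most secondary comparisons are affected. Many of those defined in the cascades section are proportions by arm, single-time results or times to linkage, and the two outcomes named for these models have no baseline.
- A reader might infer that the article contradicts itself. The implementation model serves different outcomes. It shows that the authors use baseline adjustment elsewhere, without making the other model an error.
- A reader might infer that adjustment always targets the same estimand. With the logit link planned for binary and categorical outcomes, adjusting for baseline can change the conditional odds ratio.

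**Conclusion.** The point holds in a limited form. It applies to arm comparisons on repeated outcomes with a pre-randomisation interview baseline: HIV risk behaviors, timeline followback use days, PHQ9, PROMIS, craving, stigma and the TCU Drug Screen. With the interaction in the model it is a matter of efficiency alone; without it, of attenuation to roughly 0.6 to 0.7 of a constant follow-up effect. The attenuation is the weightier reason to act, since the text makes the interaction optional.

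The sizes rest on assumed correlations of 0.3 to 0.7, the continuous-outcome formulas and complete data; the attenuation also assumes AR(1) by visit order. No single percentage fits all outcomes and visits. The primary Cox analysis and the sample size are untouched. This is a worthwhile, nearly free improvement to secondary analyses.

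**What to change.** In the longitudinal-model paragraph of the cascades section, add a rule for comparisons of PN with MHU on outcomes that have a pre-randomisation interview baseline:

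1. Take baseline out of the time factor and enter the participant's own baseline value as a covariate, as the implementation models do. Alternatively, keep baseline as a response and constrain the arm means to be equal there.
2. Use only the follow-up visits at which the outcome is collected: months 3, 6 and 12 for most of these measures. For the TCU Drug Screen, Table 1 lists month 3 but the measures text does not, so settle that first.
3. Keep the arm-by-time interaction in these models, and report the arm contrast at months 6 and 12.
4. For logit-link outcomes, state whether the reported effect is conditional or marginal.

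The cost is a change of analysis wording, best made before any comparison by arm. No new data are needed. The covariate version needs a stated way of handling missing baselines; the constrained version keeps those participants in the model.
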